## Abstract

**Background:**

Regional pain in the hip in adults is a common cause of a general practitioner visit. A considerable part of patients suffer from (greater) trochanteric pain syndrome or trochanteric bursitis. Local corticosteroid injections is one of the treatment options. Although clear evidence is lacking, small observational studies suggest that this treatment is effective in the short-term follow-up. So far, there are no randomised controlled trials available evaluating the efficacy of injection therapy.

This study will investigate the efficacy of local corticosteroid injections in the trochanter syndrome in the general practice, using a randomised controlled trial design. The cost effectiveness of the corticosteroid injection therapy will also be assessed. Secondly, the role of co-morbidity in relation to the efficacy of local corticosteroid injections will be investigated.

**Methods/Design:**

This study is a pragmatic, open label randomised trial.

A total of 150 patients (age 18–80 years) visiting the general practitioner with complaints suggestive of trochanteric pain syndrome will be allocated to receive local corticosteroid injections or to receive usual care. Usual care consists of analgesics as needed. The randomisation is stratified for yes or no co-morbidity of low back pain, osteoarthritis of the hip, or both. The treatment will be evaluated by means of questionnaires at several time points within one year, with the 3 month and 1 year evaluation of pain and recovery as primary outcome. Analyses of primary and secondary outcomes will be made according to the intention-to-treat principle. Direct and indirect costs will be assessed by questionnaires. The cost effectiveness will be estimated using the following ratio: CE ratio = (cost of injection therapy minus cost of usual care)/(effect of injection therapy minus effect of usual care).

**Discussion:**

This study design is appropriate to estimate effectiveness and cost-effectiveness of the injection therapy. We choose to use a pragmatic study design and are thus not able to study specific effects of the injection with corticosteroids. A distinction between placebo effect of the injection and specific effects of the corticosteroids is therefore not possible.

**Trial Registration:**

The trial is listed in the Dutch Trial Registry with the number ISRCTN16994576

## Background

One of the more common pain syndromes of the in the hip in adults is known as trochanteric pain syndrome (TPS) or trochanteric bursitis. It is considered to have the following characteristics: chronic, intermittent pain at the lateral site of the upper limb, sometimes radiating to the lateral aspect of the hip or lateral thigh and increasing at physical activity [1-4]. Lying on the affected site increases the pain and can thereby disturb sleep and/or rest. At physical examination palpation of the greater trochanter is painful [1-4].

The prevalence is higher among females than among males (rate 4:1) and the incidence is highest between the ages 40 to 60 years [4,5]. A recent prospective study in a Dutch general practice population showed an incidence of 5.6 patients per 1000 adults in one year (unpublished pilot data). In a retrospective study, Lievense et al. found an incidence of 1.8 per 1000 in one year [5].

Earlier, the same clinical manifestations were known as trochanteric bursitis, although clinical manifestations of inflammation almost never occur [1,2,4]. Tendinitis of the insertion of the m. gluteus medius is suggested as another cause of pain at this site. It might also be a combination of bursitis and tendinitis. Because the exact aetiology is not known, Collee et al. suggested in 1991 to classify the clinical manifestations as "greater trochanter syndrome" [6].

Observational studies showed that in most of the cases with local pain at this site co-morbidity exists. About two-thirds of the patients with TPS have also low back pain or osteoarthritis of the hip [1,3,6,7].

Many GPs inject corticosteroids combined with an anaesthetic agent at the most painful site with the expectation that the pain will decrease. There is no conclusive evidence that these injections are effective, although small observational studies suggest that injections with corticosteroids are effective in the short-term follow-up [2,5,7,8]. No randomised controlled trials are available evaluating the benefit of injection therapy for this disorder. Other common treatment options are pain relief with analgesics, physiotherapy, a surgical release of the iliotibial tract, removal of the bursa, or a trochanteric reduction osteotomy [9].

This study we will investigate the efficacy and cost effectiveness of local corticosteroid injections in TPS, using a randomised controlled trial design. We also investigate the role of co-morbidity in relation to the efficacy of this local corticosteroid injection.

## Methods/Design

### Study design

This study is a pragmatic, open label randomised trial.

The local Medical Ethics Committee of the Erasmus University Medical Center, Erasmus MC, has approved the trial. The trial is included in the Dutch Trial register (ISRCTN 16994576).

All patients will give written informed consent.

### Patient selection

GPs participating in the HONEUR research network of the Erasmus MC and other interested GPs in the area will be invited to participate in the study. The HONEUR GP research network consists of 40 GP practices which are connected to the Department of General Practice in order to participate in regular research projects. They will be asked to select patients aged 18 to 80 years visiting the GP with the following symptoms: pain persisting for more than one week in the lateral region of the hip or thigh with tenderness at palpation of the greater trochanter with one of the two following characteristics [1-4,10]:

1). Severe pain at palpation of the greater trochanter, but uncertainty as to whether the patient recognizes the pain as that for which he or she visits the GP.

2). Local tenderness when the area of the great trochanter is palpated and the patient recognizes the pain as that for which he or she visits the GP.

Excluded are patients who are unable to understand the Dutch questionnaires, patients who have consulted the GP with the same complaints in the previous year and had any intervention, or are operated on in the same region, or have systemic neurological or rheumatologic disorders.

### Procedures

Patients who are eligible for the study and show interest to participate will receive written study information from their GP, as well as the baseline questionnaire and the informed consent form. If they show interest the GP will fax their contact data to the researcher together with the findings of physical examination on a standardized form. One of the investigators will contact the patient to ask if they have any additional questions and will assess the suitability to participate in the study. If the patient still wants to participate and is eligible, we ask them to return the baseline questionnaire and informed consent form.

When we receive the baseline questionnaire, the patient will be classified as having comorbidity or not. If the question: "Do you suffer from low back pain" is answered positively as often or continuous, we classify the patient as having low back pain comorbidity. The ACR criteria for osteoarthritis of the hip, using history and physical examination (painful or decreased internal rotation and flexion of the hip as performed by the GP) are used to decide whether the patient has osteoarthritis of the hip as comorbidity [11].

### Randomisation

After receiving the baseline questionnaire and informed consent, an independent person will randomise each patient based on computerized randomisation lists to either receive the injection therapy or the usual care, consisting of analgesics as needed. This randomisation is stratified for yes or no comorbidity and uses randomisation block sizes of ten, yielding four strata: one lacking comorbidity, one with low back pain, one with osteoarthritis, and one stratum with both.

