### Sample size

The sample size was calculated to detect an increase in recovery rate of 25% in the intervention group after three months of follow-up (45% recovery in the control group versus 70% recovery in the intervention group). With power 0.8 and alpha 0.05 (two-sided tested) and with a dropout rate of 10%, a total number of 75 patients in each group are needed.

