### Data analyses

Difference between the groups in the primary outcome will be analysed based on the basis of the "intention-to-treat" principle. Differences in continuous outcome measures between the groups will be analysed with linear regression techniques and differences in dichotomous outcomes (recovery dichotomised to totally recovered or almost totally recovered versus slightly recovered and less) will be analysed with logistic regression techniques. Baseline differences between the groups will be assessed and checked whether these influence the outcome of the study. Baseline variables that change the outcome by 10% or more will be regarded as confounders and will therefore be added to the regression models.

Regression models will also be used to study effect modification of comorbidity. A cost-effectiveness analyses will be performed from a social and a patient perspective, looking at differences in direct and indirect health care cost between the two groups.

If the trial does not show a difference in disease parameters (VAS and WOMAC) and quality of life (EuroQol) between the groups, the analysis will be reduced to a cost minimisation analysis. This form of analysis evaluates the efficacy of treatment based solely on direct and indirect costs. If the study does find a positive difference in disease parameters and/or quality of life in the injection group, a cost-effectiveness ratio can be determined.

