## Discussion and current status

In this study design we compare two types of therapy which are frequently used in general practice. This study design is appropriate to estimate effectiveness and cost-effectiveness of the injection therapy. We choose to use a pragmatic study design and are thus not able to study specific effects of the injection with corticosteroids. A distinction between placebo effect of the injection and specific effects of the corticosteroids is therefore not possible.

The study is executed in general practice and may therefore not apply to patients in secundary care.

No disease specific questionnaires are available for this disorder. Therefore generic outcome measures (recovery and pain severity) were chosen as primary outcome measures. However, region specific questionnaires for osteoarthritis were included as secondary outcome measures. These questionnaires allow us to analyse subscales like for instance the WOMAC pain and the WOMAC function; subsequently osteoarthritis specific questions on stiffness (WOMAC stiffness) can validly be omitted.

Patients included in our trial have symptoms of TPS solely, or have these symptoms in co-occurrence with low-back pain or osteoarthritis of the hip. To include patients with such co-morbidity maybe questionable because the TPS may be due to such morbidity. Therefore injection therapy for TPS in such morbidity possibly shows different effectiveness. We chose to include these patients because in common practice these patient also receive injection therapy. We, however, used a design in which we stratify for co-morbidity or not.

The current status of the study is that of a total of the 80 GPs participating in the study. However, until now only 43 GPs included 90 patients. The total study population is expected to be recruited by February 2008. The first short-term results (3 months of folluw-up) will be available at mid-2008.

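### Randomisation is stratified by comorbidity, but the strata enter the primary models only through a 10% change-in-estimate rule that suits a factor balanced by design badly

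*Protocol article*

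**What the plan says.** The Randomisation section states: "This randomisation is stratified for yes or no comorbidity and uses randomisation block sizes of ten, yielding four strata". The strata are "one lacking comorbidity, one with low back pain, one with osteoarthritis, and one stratum with both". The Abstract, the Procedures section and the Discussion describe comorbidity as present or absent; the Discussion has "We, however, used a design in which we stratify for co-morbidity or not".

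The Data analyses section names linear regression for continuous outcomes. Recovery, dichotomised, "will be analysed with logistic regression techniques". Neither model is said to contain the strata. The stated route for a baseline variable into a model is a change of 10% or more in the outcome comparison, in which case it counts as a confounder and is added. Comorbidity has one other stated use: "Regression models will also be used to study effect modification of comorbidity".

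**The concern.** A change-in-estimate rule looks for confounding, that is, for a prognostic variable that is unevenly spread between the arms. Blocking within strata makes comorbidity nearly even by construction. In a linear model the rule then says little about whether comorbidity predicts the outcome, and a strongly prognostic stratum can fail it.

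If such a stratum is left out, the variation between strata stays in the residual variance although the design has removed it from the sampling error of the treatment estimate. The reported standard error is too wide, the test is conservative, and some of the benefit of stratifying is lost.

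The logistic model behaves differently. The odds ratio moves on adjustment for a prognostic factor even under perfect balance, so the same rule may admit the strata there. The two primary outcomes could then be analysed with different adjustment, and the kind of odds ratio reported would be decided by the data.

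**Working it through.** **1. The plan's own figure.** Inputs from the Sample size section: "45% recovery in the control group versus 70% recovery in the intervention group", power 0.8, two-sided alpha 0.05, dropout 10%.

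- Pooled formula: n = [1.96·√(2·0.575·0.425) + 0.8416·√(0.45·0.55 + 0.70·0.30)]² / 0.25² = (1.370 + 0.569)² / 0.0625 ≈ 60.2, so 61 per arm.
- With continuity correction: (60.2/4)·[1 + √(1 + 4/(60.2·0.25))]² ≈ 68 per arm.
- With dropout: 68 × 1.1 = 74.8, so 75; or 68/0.9 = 75.6, so 76.

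The stated "a total number of 75 patients in each group are needed" is reproduced. It is an unstratified two-proportion calculation, and the point below does not change it.

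**2. Assumptions for the rest.** The documents give no outcome by comorbidity and no SD for pain. Assumed: 136 analysed patients (150 less 10% is 135, rounded to equal arms of 68); strata of 46/30/30/30 for none, low back pain, osteoarthritis, both, in line with the Background's statement that about two-thirds have comorbidity; blocks of ten; within-stratum pain SD 2.5; treatment difference 1.2 points.

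**3. Pain, linear model.** With stratum shares w and shifts s, the between-stratum variance is V = Σws² − (Σws)². The unadjusted SE exceeds the adjusted one by the factor √(1 + V/2.5²). The adjusted SE is 2.5·√(4/136) = 0.429.

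| Assumed shifts | V | SE factor | Unadjusted SE | Type I error without strata | Power without / with strata |
|---|---|---|---|---|---|
| 0/1/1/2 (moderate) | 180/136 − (120/136)² = 0.545 | 1.043 | 0.447 | 4.1% | 77.5% / 79.9% |
| 0/2/2/4 (steep) | 4 × 0.545 = 2.180 | 1.161 | 0.498 | 2.3% | 69.9% / 79.9% |

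With f the SE factor, type I error is 2·[1 − Φ(1.96·f)]. Power without strata is Φ((1.2 − 1.96·0.429·f)/0.429), because the blocked estimate still has a sampling SD near 0.429. Simulation agrees: SE 0.446 and about 0.50 against 0.43; type I error 3.9% and about 2.5%; power 77% against 79% (moderate) and 70% against 79% (steep). With a different assumed mix (33/33/17/17%) the SE excess was 2–4% and about 14%. With no stratum effect the SEs were 0.429 and 0.430.

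**4. Would the 10% rule admit the strata for pain?** Ten per cent of 1.2 is 0.12 points. Take an arm difference of D patients in the stratum with both conditions. It moves the estimate by D·(2 − 0.88)/68 = 0.0164·D in the moderate case, so D must be about 7; in the steep case it must be about 4. A block of ten allows a difference of at most 5, and none once the block is complete. In simulation with a true effect the rule admitted the strata in 1–5% of trials.

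**5. Recovery, logistic model.** Assumed conditional odds ratio 2.85 and control recovery 65/40/35/25% (moderate) or 75/35/30/15% (steep). Averaging over strata with perfect balance:

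- Moderate: 44.0% against 67.0%, marginal odds ratio 2.58; 2.85/2.58 = 1.105, a change of about 10%.
- Steep: 43.0% against 63.1%, marginal odds ratio 2.27; 2.85/2.27 = 1.26, a change of about 26%.

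So the rule can be met with no imbalance at all. Simulation (4,000 trials each, rule applied on the log-odds or odds-ratio scale):

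| | Rule admits strata | Power, never adjusted | Under the rule | Always adjusted | SE of log odds ratio, without / with strata |
|---|---|---|---|---|---|
| Moderate | 61–66% | 77.7% | 80.4–81.6% | 82.1% | 0.358 / 0.388 |
| Steep | 91–98% | 66.4% | 75.2% | 75.3% | 0.353 / 0.417 |

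Adjustment raises this SE; power improves because the conditional estimate is larger.

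**The case against.** The strongest case against runs as follows.

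- **The text nowhere excludes the strata, and a condensed article may leave the covariate list to the analysis plan.** True. A reader might infer that the primary models leave the strata out; the documents do not say so. What stands is that the article does fix a rule for covariates, and that rule handles this factor badly.
- **The loss for recovery is largely illusory.** This stands. A reader might set the never-adjusted test beside the always-adjusted one and infer a loss of about 4 to 9 points on the outcome that sizes the trial. The plan does not describe a never-adjusted test, and its own rule recovers nearly all of that power. If the rule is read narrowly, as covering only variables that differ at baseline, the strata would be admitted less often.
- **The excess in the SE is conditional.** This stands. If comorbidity is not prognostic there is nothing to gain. Under a mild assumed gradient for recovery (52/45/42/36%), power was 83.6% against 84.4%.
- **Two against four strata is not a contradiction.** This stands. Procedures defines low back pain and hip osteoarthritis separately, and yes/no for each gives 2 × 2 = 4. It is loose wording to tidy.
- **The error is conservative.** This stands. There is no bias and no excess of false positives.

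**Conclusion.** The point holds in limited form: the stratification factor depends on a data-driven rule that is unsuited to it.

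For pain, prognostic strata would seldom be admitted. The SE would then be about 4% (moderate) to 16% (steep) too wide, and power lower by about 2 points to about 9 (10 by the closed form). These sizes rest on the assumed SD, treatment difference, stratum mix and stratum effects. The assumed stratum sizes also include three made up of complete blocks. Dropout would unsettle the balance and let the rule admit the strata more often, so the steep-case loss is nearer an upper end.

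For recovery, little power is at stake. The defect there is that the data would decide whether the odds ratio is marginal or conditional, and that adjustment could differ from that for pain.

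The documents do not support saying that standard errors are certainly too wide, that adjusting narrows the logistic SE, or that the descriptions of the strata contradict each other. The sample size of 75 per group is unaffected.

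**What to change.** - In Data analyses, prespecify the stratum as randomised (none, low back pain only, hip osteoarthritis only, both) as a fixed covariate in all primary and secondary treatment models, linear and logistic, regardless of the 10% rule.
- State that the recovery odds ratio is then conditional on stratum.
- Study effect modification separately, with a treatment-by-comorbidity interaction term, and say whether comorbidity has two or four levels there.
- Describe the strata identically in the Abstract, Procedures, Randomisation and the Discussion.

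The cost is wording and three degrees of freedom. If comorbidity is not prognostic, essentially nothing is lost: simulated power with and without strata was 79.2% and 79.1% for pain, and 85.5% either way for recovery. A very small stratum could make a logistic fit unstable. Under the largest simulated log-odds shifts (0/−1/−1/−2, no treatment effect), 46 of 4,000 fits (1.2%) had to be set aside, so a fallback for sparse strata is worth one sentence.

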### Intervention

The GP and the patient will be informed about the treatment that the patient will be given as soon as randomisation has taken place. The GPs participating in the study have been trained by us to give the injection according to a standard procedure: i.e. to use 40 mg triamcenolon acetate combined with lidocaine 1 or 2% in a 5 ml syringe. They are trained to mark the most painful point with a pen or pencil and desinfect the site. The needle is inserted perpendicular to the skin and directed down to the point of maximal tenderness, 1 ml of the substance will be injected at that point, then the needle should be moved to another place in the painful area and the same procedure should be repeated until the syringe is empty. In case of lack of efficacy, or only temporary effect, this procedure may be repeated after a period of 3 weeks up to 3 months

After the injection the GP will fax us a form with details of the injection given, e.g. the volume that is injected, if the injection was painful, or if there was pain relief after injection or direct side effects.

The control group will receive usual care consisting of analgesics as needed; all patients are free to receive additional treatment from a physiotherapist, although this is not advocated by the investigators.

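### With a fixed block size of ten in an open-label trial, study staff who classify patients and also see injection forms could foresee a few allocations

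*Protocol article*

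**What the plan says.** All references are to the protocol article.

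- **Study design:** "This study is a pragmatic, open label randomised trial".
- **Randomisation:** the procedure "uses randomisation block sizes of ten, yielding four strata". The strata are "one lacking comorbidity, one with low back pain, one with osteoarthritis, and one stratum with both". Practice is not a stratification factor, so each list runs centrally across all GPs. The lists are in separate hands: "an independent person will randomise each patient based on computerized randomisation lists".
- **Procedures:** the GP's examination findings reach the researcher at referral. An investigator then "will contact the patient to ask if they have any additional questions and will assess the suitability to participate in the study". The baseline questionnaire is returned after that contact, and the study team uses it to assign the stratum: for a given answer on back pain, "we classify the patient as having low back pain comorbidity". Hip osteoarthritis is decided by the ACR criteria from history and the GP's examination. Both steps come before randomisation.
- **Intervention:** "After the injection the GP will fax us a form with details of the injection given". GP and patient learn the allocation once it is made.
- **Questionnaires and Table 1:** injected patients are asked about side effects of the injection from 6 weeks on.
- **Discussion and current status:** 90 of the planned 150 patients had been included, by 43 GPs.

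**The concern.** An independent list-holder conceals the list itself. That does not stop someone who knows the block length, the stratum and the past allocations from working out how a block must end. Here the team that admits and classifies patients is also the team to which injection forms are returned.

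If a coming allocation can be inferred, the decision to admit a patient, or the stratum a patient is placed in, could be influenced by it. That is selection bias. It matters in this trial for three reasons:

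- Both primary outcomes, experienced recovery and pain, are reported by patients who know their treatment.
- Comorbidity is the stratification factor and also the planned effect modifier, so a steered classification would touch the subgroup question as well.
- The planned adjustment for baseline variables that change the outcome by 10% or more cannot correct for features that were not measured.

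**Working it through.** The article gives no predictability figure to reproduce, and its sample size does not depend on this point.

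**Inputs**

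- Block of 10, taken as 5:5 because the plan has 75 patients per group (Randomisation; Sample size).
- Four strata (Randomisation). Their sizes are not given. Assumption: they range from 38 patients, close to 150/4, to exact multiples of ten.
- Patients still to be recruited: 150 − 90 = 60 (Discussion and current status).
- Assumption: one person tracks allocations by stratum.

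**1. Certain allocations, everything known at once.** With j allocations of the block visible, the next is certain if one arm has used its five places. The probability is 2·C(j,5)/C(10,5), with C(10,5) = 252. For j = 5, 6, 7, 8, 9 the numerators are 2, 12, 42, 112 and 252, which sum to 420. Expected certain allocations per block: 420/252 = 1.67 of 10, or 16.7%. The general formula 2m/(m+1) with m = 5 gives the same: 10/6.

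**2. Incomplete last block.** A stratum of 38 has three full blocks and eight places of a fourth: (3 × 420 + 56)/252 = 5.22, and 5.22/38 = 13.7%. Simulation of 150 patients under four assumed stratum splits gave 13.6–16.6%.

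**3. Recent allocations not yet known.** If the last k are unknown, j stops at 9 − k.

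- Full blocks: 168/252 = 0.67, 56/252 = 0.22 and 14/252 = 0.06 of 10, for k = 1, 2, 3.
- Stratum of 38: (3 × 168 + 14)/252 = 2.06, (3 × 56 + 2)/252 = 0.67 and (3 × 14)/252 = 0.17 of 38.

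| Latest allocations unknown | Share certain | Of 60 patients |
|---|---|---|
| 0 | 13.7–16.7% | 8.2–10.0 |
| 1 | 5.4–6.7% | 3.2–4.0 |
| 2 | 1.8–2.2% | 1.1–1.3 |
| 3 | 0.4–0.6% | about 0.3 |

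The last column applies the overall rates to 60 patients. It is approximate, because some blocks are already part-used.

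**4. Best guess.** Guessing the arm that is behind is right in 5 + (2^10/252 − 1)/2 = 6.53 of 10, or 65%, against 50% by chance. In simulation the rate falls to about 60%, 58% and 55–56% when one, two or three recent allocations are unknown.

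**5. Varying, undisclosed block sizes.** Simulation of a 38-patient stratum (4,000 runs):

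| Scheme | Certain | Guessed right |
|---|---|---|
| Fixed 10 | 13.8% | 64.2% |
| Random 6/8/10 | 0.03% | 65.7% |
| Random 8/10/12 | 0.006% | 64.4% |

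Certainty practically disappears, but guessing does not improve. Smaller blocks (4/6/8) are guessed right slightly more often, at about 67–68%.

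**6. Order of events.** Suitability is judged before the baseline questionnaire comes back, so the back-pain part of the stratum is not yet recorded. Other patients may also be randomised in the meantime. At classification the stratum becomes known, and randomisation follows. Classification is therefore the better-informed point.

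**The case against.** The case for leaving the design alone is substantial, and much of it stands.

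- **Delay.** A form arrives only after an injection. Usual care has to be inferred from a missing form, which looks the same as an injection not yet given. This stands, and it is why the 8–10 of 60 is a ceiling rather than an estimate.
- **Little room to steer.** Back pain depends on a fixed questionnaire answer, and osteoarthritis on published criteria with the GP's examination. This stands and limits the risk further, though it does not remove it.
- **Who sees what.** A reader might infer that the same people screen, classify and read the forms. The text says only that one of the investigators makes contact, and otherwise speaks of the team in the first person plural. The overlap is an assumption. The full protocol, which is not shown, may separate the tasks.
- **Publication.** A reader might infer that printing the block size mid-recruitment created the problem. The investigators wrote the article and learn nothing from it. GPs could learn the size, but they average 90/43 = 2.1 patients each and the lists are not per practice.
- **Limited remedy.** Varying block sizes alone leave guessing as easy as before. Re-routing only the injection form would leave the side-effect reports as a second source. Both points stand, and the fix takes account of them.

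The independent list-holder, by contrast, does not answer the concern: inference from past allocations does not need the list.

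**Conclusion.** The point holds as a modest risk that is cheap to reduce. It is neither an error nor a contradiction, since a block of ten with an independent allocator is a defensible choice. The weakness is the combination of one fixed block length, open treatment, and forms showing past allocations sent back to the team that screens and classifies.

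The size depends on two assumptions: that the staff who screen or classify also see the forms, and how quickly they learn earlier allocations. The upper bound is about 14–17% of allocations certain. With a realistic delay it is a handful of the remaining patients or fewer.

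A reader might go further and conclude that allocation concealment failed, that the suitability decision is as exposed as the classification, or that the results are biased. The document supports none of these: the lists are held independently, the stratum is only partly known when suitability is judged, and nothing shows that anyone acted on a prediction.

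**What to change.** **Main step, for the remaining patients.** Keep earlier allocations, and the block length of any further list, from whoever assesses suitability and assigns the stratum. Send injection forms and injection side-effect reports to the independent person, or to a team member with no part in screening or classification. Safety information then still reaches the study team. Because the present block length is already in print, withholding past allocations is what protects the lists now in use.

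**Secondary step.** Have the independent person generate the remaining lists within the same four strata with randomly varying block sizes, undisclosed until recruitment ends. This removes practically all certain predictions but leaves guessing from the running imbalance right about 64–66% of the time, so it does not replace the main step.

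**Cost.** Re-routing of forms and new computer-generated lists, plus a slight extra risk of imbalance when up to four part-used blocks are closed. No extra staff or patients are needed.
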